### Quality control

All acupuncturists are required to receive special training, including the technique for catgut implantation and the way to deal with adverse events. The acupuncturists should also learn how to use the randomization method in order to communicate with patients and to keep them blind to the treatment throughout the trial. Only those who have completed the required training and have passed all necessary examinations will be recruited for this trial. In order to maintain quality of this trial, all outcome assessments will be blinded. In addition, all researchers must understand the purpose and design of this trial. Audits will be conducted regularly on compliance with standard operation procedures every week. Report of audits should be presented to the chief monitor. If patients withdraw from the trial either in the treatment period or in the follow-up phase, the reason should be clarified and the rate should be analyzed in statistics.

### Statistical analysis

In our preliminary study to compare the efficacy of catgut implantation at acupoints with intranasal glucocorticoid, it was suggested that efficiency was 93.75% in the catgut implantation group and 96.88% in the control group. In this study, we anticipate an improvement of no less than 15% after real catgut implantation at acupoints. However, there are no previous data regarding the VAS or RQLQ scores for the treatment of AR with catgut implantation at acupoints. Considering participants recruited in the two groups are in a 1:1 ratio, the following formula was used to estimate sample size [13]:

$$n_{1}=n_{2}={\left[\frac{Z_{\alpha }\sqrt{2\pi_{c}\left(1-\pi_{c}\right)}+Z_{\beta }\sqrt{\pi_{1}\left(1-\pi_{1}\right)+\pi_{2}\left(1-\pi_{2}\right)}}{\pi_{1}-\pi_{2}}\right]}^{2}$$

In the formula: n1, n2 represents the sample size of each group. π1, π2 is the overall rate of each sample, respectively. πc = (π1 + π2)/2, α = 0.05, Z_0.05_ = 1,96,β = 0.10,Z_0.10_ = 1.282. Statistical analysis will be performed using a 5% significance and 90% power, resulting in an estimated 121 patients per group.

To test our hypothesis, the first step is to assess the baseline characteristics of two groups using an unpaired *t* test or *x*^2^ testes. The second step is to compare the efficacy of real catgut implantation with the sham one, including the primary and secondary outcomes using two-sample t test. If there is any case lost in follow-up phase or withdrawn from the trial, the causes of withdrawal should be clarified. The intention-to-treat analysis (ITT) and per-protocol (PP) analysis should be conducted to test whether the result of this trial is credible. For relief medication, within-group as well as between-group comparisons of scores are to be made. Data will be analyzed using the Statistical Package for the Social Sciences software, version 15.0 for Windows (SPSS Inc., Chicago, IL, USA). Data are presented as mean and 95% confidence intervals (CI). The statistical analysis will be performed in a blinded manner by qualified statisticians.

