**Methods and design:**

This study compares real *versus* sham catgut implantation at acupoints in 242 patients with a history of PER or IAR and with a positive skin prick test (SPT). The trial will be conducted in the Teaching Hospital of Chengdu University of Traditional Chinese Medicine. In the study, patients will be randomly assigned by computer-generated randomization list into two groups and assessed prior to treatment. Then, they will receive two sessions of treatments (once per 2 weeks) for 4 consecutive weeks and have a follow-up phase of 12 weeks. The administration of catgut implantation (or sham-control) at acupoints follows the guidelines for clinical research on acupuncture (WHO Regional Publication, Western Pacific Series No.15, 1995), and is performed double-blindly by a well-trained physician in acupuncture. The main outcome measures include the primary and secondary indicators. Primary indicators are subjective symptoms scores evaluated by visual analogue scales (VAS) and Rhinoconjunctivitis Quality of Life Questionnaires (RQLQ). The secondary indicators are the results of laboratory examinations, such as serum allergen-specific IgE, nasal inflammatory cells counts (mast cells, eosinophils, and T cells) and nitric oxide concentration in nasal excretion. The use of anti-allergic medication will also be recorded as one of the secondary indicators. Furthermore, adverse events will be recorded and analyzed. If any participants withdraw from the trial, intention-to-treat analysis (ITT) and per-protocol (PP) analysis will be performed.

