#### Withdrawal from the study

Study patients will be allowed or be asked to withdraw from the study if:

(1) they have been included in the trial but would not subject to the assigned treatment for varies reasons at any of the stages of the trial

(2) severe adverse events occur that necessitate withdraw of patients from the trial

(3) they do not fully participate in treatment or follow-up

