### Trial status

The recruitment of patients started June 1,2012, and it is expected that by March 31, 2013 the required sample size will be reached.

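### The 121 per group equals the formula's result with no loss term and is also the number enrolled, so on the best-fitting reading the stated 90% power assumes complete outcome data

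*Protocol article*

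**What the plan says.** The Statistical analysis section of the protocol article prints a two-proportion sample size formula with "α = 0.05, Z_0.05_ = 1,96,β = 0.10,Z_0.10_ = 1.282" and concludes: "Statistical analysis will be performed using a 5% significance and 90% power, resulting in an estimated 121 patients per group".

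Two figures there could feed the formula. One is the pilot result, "efficiency was 93.75% in the catgut implantation group and 96.88% in the control group", where the control was an intranasal glucocorticoid. The other is the target effect, "we anticipate an improvement of no less than 15% after real catgut implantation at acupoints". The values entered for π1 and π2 are not printed, and the text does not say whether the 15% is absolute or relative.

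The abstract (Methods and design) describes a comparison of real and sham "catgut implantation at acupoints in 242 patients with a history of PER or IAR". Trial status says of recruitment that "it is expected that by March 31, 2013 the required sample size will be reached".

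On losses, the section on withdrawal allows or asks patients to leave if, among other reasons, "they do not fully participate in treatment or follow-up". Quality control asks for the reasons for withdrawal and an analysis of its rate. The Statistical analysis section adds: "The intention-to-treat analysis (ITT) and per-protocol (PP) analysis should be conducted to test whether the result of this trial is credible". No expected loss rate and no inflation of the sample size appear anywhere in the article.

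**The concern.** A formula of this kind gives the number of patients who must contribute an outcome. Here that number and the number enrolled are the same: 121 per group, 242 in all. If 121 is the direct result of the formula, the 90% describes a trial in which every enrolled patient is analysed. The article has 4 weeks of treatment and 12 weeks of follow-up after randomisation, a withdrawal rule that covers incomplete participation, and a per-protocol analysis used to judge credibility. Once patients are lost, the per-protocol set, and any comparison of scores observed at the end of follow-up, falls below 121 per group.

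What is at stake is how the result is read. A null finding, or a per-protocol result that disagrees with the intention-to-treat result, would be taken to come from a 90%-powered comparison when the analysed set may have somewhat less.

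**Working it through.** **Inputs.** From the Statistical analysis section: z for α = 1.96, z for β = 1.282, pilot catgut rate 93.75%, improvement 15%, 1:1 allocation. From the abstract: 242 enrolled. Loss rates are assumptions, because the article gives none.

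**Formula as printed.** n per group = {[1.96·√(2πc(1−πc)) + 1.282·√(π1(1−π1) + π2(1−π2))] / (π1−π2)}², with πc = (π1+π2)/2.

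**Step 1: reproduce 121.** Take π1 = 0.9375 and π2 = 0.9375 × 0.85 = 0.7969.
- πc = 0.8672, and √(2πc(1−πc)) = √0.2303 = 0.4799
- √(π1(1−π1) + π2(1−π2)) = √0.2205 = 0.4695
- π1−π2 = 0.1406
- n = [(1.96 × 0.4799 + 1.282 × 0.4695) / 0.1406]² = [(0.9407 + 0.6019) / 0.1406]² = 120.3, rounded up to 121

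This matches the printed figure with no loss term. Doubling gives 242, the number enrolled.

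**Step 2: other readings of the 15%.**

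| Rates entered | Formula result | Power at 121 per group |
|---|---|---|
| 93.75% vs 79.69% (15% relative reduction) | 120.3 → 121 | 90.2% |
| 93.75% vs 78.75% (15 points absolute) | 108.7 → 109 | 92.8% |
| 93.75% vs 81.52% (93.75%/1.15, relative gain over sham) | 150.2 → 151 | 82.8% |

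Of these, only the first returns 121 directly. The second reaches it with a further step: 108.7 / 0.9 = 120.8, rounded up to 121, which is a 10% allowance.

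**Step 3: power after loss.** Solve the same formula for z for β with m patients analysed per group: z = [(π1−π2)√m − 1.96·√(2πc(1−πc))] / √(π1(1−π1) + π2(1−π2)), and power = Φ(z). For example, at 10% loss m = 121 × 0.90 ≈ 109. On the relative reading z = (0.1406 × √109 − 0.9407) / 0.4695 = (1.4682 − 0.9407) / 0.4695 = 1.123, so power is 86.9%.

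| Assumed loss | Analysed per group | Power, 93.75% vs 79.69% | Power, 93.75% vs 78.75% |
|---|---|---|---|
| 0% | 121 | 90.2% | 92.8% |
| 5% | 115 | 88.7% | 91.6% |
| 10% | 109 | 86.9% | 90.1% |
| 15% | 103 | 85.0% | 88.4% |
| 20% | 97 | 82.8% | 86.4% |

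On the first reading power is already 89.9% at 120 per group, so the rounding leaves less than one patient per group in reserve.

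**The case against.** The strongest objection is that the absence of a reserve is inferred. Neither rate is printed, and 15 percentage points is a natural reading of the target. That reading gives 108.7, and a conventional 10% allowance brings it to 121. A reader might conclude from the match in step 1 that the plan certainly has no reserve and that the 90% fails as soon as anyone is lost. The article does not support anything so firm: on the absolute reading, power is still about 90% at 10% loss. This part of the objection stands. Against it, the article presents 121 as what the calculation yields and mentions no inflation, so the direct relative reading remains the better fit.

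A second objection is that the provisions on loss are mostly conditional. They say what happens if patients withdraw and predict no rate. A reader might infer that the plan expects a particular shortfall, or that the 90% was promised for the per-protocol set. Neither is stated. An intention-to-treat analysis could also keep all 242, though only by filling in missing outcomes. What remains is narrower: one power figure is given, without saying which number of analysable patients it belongs to.

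Third, a journal article may leave a loss assumption to the full protocol. That would excuse silence. But this article prints the formula, the z values, the result and an unqualified 90%, so the condition on that figure belongs beside it.

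Finally, the 90% concerns a binary efficiency rate, while the primary outcomes are VAS and RQLQ scores compared by t test. That is a separate matter. It does mean that the figures above describe the plan's own calculation and are not the power of the primary analysis.

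**Conclusion.** The point holds in a limited form. On the reading that best fits the text (93.75% vs 79.69%, no inflation), the stated 90% applies only if all 121 per group contribute an outcome. Under assumed losses of 5% to 20%, power falls to between about 88.7% and 82.8%, which is a modest shortfall. It rests on two assumptions: the rates entered, which are not printed, and the loss rate, which is not given. If the 15% is absolute and an unstated 10% allowance was added, power is about 90% at 10% loss and 88% at 15%. The article does not allow the reader to tell these cases apart, and that is itself part of the defect. The finding does not show that the trial is too small or that more patients must be enrolled.

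**What to change.** Keep 242 enrolled. In the Statistical analysis section:

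- State the two rates entered as π1 and π2, and whether the 15% is absolute or relative.
- State that 121 per group is the number needed with complete outcome data or, if an allowance was used, state it.
- Replace the unconditional 90% with the power at the number expected to be analysable. On the relative reading this would be, for example, about 87% at 10% loss and 85% at 15%, with the assumed loss rate named.

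The cost is one or two sentences and a slightly less favourable stated power. Recruitment and conduct do not change.

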## Methods and design

### Study design

This study will be a double-blind, randomized, sham-controlled trial conducted in the Department of Otorhinolaryngology-head and neck surgery, Teaching Hospital of Chengdu University of T.C.M., China. This study includes the following time points: a run-in period of 4 weeks after screening, a treatment period of 4 weeks, and a follow-up period of 12 weeks. The total study period will be 20 weeks. At the screening visit, medical history especially in relation to AR and other allergic diseases will be asked and recorded by a study physician based on a systemically designed questionnaire. Patients who satisfy the inclusion criteria will be recruited into the run-in period. After randomization, patients will be blindly assigned to either the real catgut implantation at the acupoints group or the sham group (controls). All patients will receive two treatments over a period of 4 weeks. Chlorphenyramine will be used as a rescue medication if the patients present with untolerable AR symptoms. At the same time, patients should complete visual analogue scales (VAS) [9] and Rhinoconjunctivitis Quality of Life Questionnaires (RQLQ) [10,11] before randomization, at the end of treatment, during and after the follow-up period, respectively. Meanwhile, inflammatory cells and mediators in nasal secretions will also be measured at these three visits. Outcome measurements will be assessed by evaluating the efficacy and safety of catgut implantation at acupoints in the treatment of AR.

The design of this study followed the guidelines of the Helsinki Declaration (Version Edinburgh 2000) and was approved by Sichuan Regional Ethics Review Committee on Traditional Chinese Medicine (TCM). Informed consent are to be obtained from all the study patients. Before signing the consent, all patients will be given enough time to decide whether to participate in the trial. Other treatment options instead of catgut implantation at acupoints will be available for those who are unwilling to be recruited in the study.

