### Outcome measurements

#### Primary outcome

The primary outcome measures will be the severity of the AR symptoms assessed by (VAS) [9] and the RQLQ [10,11]. In VAS, the severity of the combination of the nasal symptoms will be subjectively rated by the study patients on the scale. The severity of symptoms can be divided into mild, moderate, or severe based on the total severity VAS score (0 to 10 cm: mild, VAS 0–3; moderate, VAS 3.1-7; severe, VAS 7.1-10). VAS scores will be recorded every 2 weeks during the whole trial. Influence of AR on QOL will be measured by questionnaire every 4 weeks: at baseline, at the end of treatment, during the follow-up period, and at the end of follow-up period (a total of five times). Both the scores of VAS and RQLQ questionnaire will be blindly assessed.

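### VAS and RQLQ are to be compared by a two-sample t test with no baseline covariate, although both are scored before randomization; the test is valid but gives up precision

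*Protocol article*

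**What the plan says.** The Statistical analysis section of the protocol article sets out two steps. In it, "the first step is to assess the baseline characteristics of two groups using an unpaired" t test, or chi-square tests. The next part of the plan reads: "compare the efficacy of real catgut implantation with the sham one, including the primary and secondary outcomes using two-sample t test". The article names no covariate, analysis of covariance or repeated-measures model, and it states no consequence of the baseline tests. It also does not say whether the t test is applied to final scores or to changes from baseline.

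The baseline values will be available. Under Study design, "patients should complete visual analogue scales (VAS) [9] and Rhinoconjunctivitis Quality of Life Questionnaires (RQLQ) [10,11] before randomization" and again at later times. Under Primary outcome, RQLQ is scheduled "at baseline, at the end of treatment, during the follow-up period, and at the end of follow-up period (a total of five times"), and "VAS scores will be recorded every 2 weeks during the whole trial". The trial consists of "a run-in period of 4 weeks after screening, a treatment period of 4 weeks, and a follow-up period of 12 weeks".

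**The concern.** A patient's VAS or RQLQ score before treatment will usually predict the later score. Eligibility sets no minimum VAS, and both persistent and intermittent rhinitis are enrolled, so a wide spread at baseline is to be expected. A t test on final scores leaves that spread in the error term. A t test on change scores uses baseline, but with a fixed slope of one, which is less precise than a fitted slope and over-corrects chance imbalance.

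The planned baseline test does not fill the gap. Under proper randomization any baseline difference arises by chance, so a p-value for it tells the analyst nothing useful, and the plan attaches no action to it.

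Precision matters in this trial. The sample size comes from a response rate, and the article says that no earlier VAS or RQLQ data exist for this treatment, so power for the actual primary outcomes is unknown. The sham punctures the same points with the same needle, and the Discussion allows that it may have effects of its own, so the difference between groups could be small.

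**Working it through.** **Plan's own figure.** The article states: "Statistical analysis will be performed using a 5% significance and 90% power, resulting in an estimated 121 patients per group". Its constants are "α = 0.05, Z_0.05_ = 1,96,β = 0.10,Z_0.10_ = 1.282", that is, a two-sided 5% test. The two rates are not printed. Taking π1 = 0.9375 (the pilot catgut rate) and reading the 15% as relative, π2 = 0.85 × 0.9375 = 0.7969 and πc = 0.8672. The printed formula then gives

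[(1.96 × √0.2303 + 1.282 × √0.2205) / 0.1406]² = (1.5426 / 0.1406)² = 120.3, rounded up to 121.

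This matches, although the relative reading is inferred; 15 points absolute (0.9375 against 0.7875) gives 109. The figure concerns a binary rate, so it says nothing about power for VAS or RQLQ. It is used below only as the group size.

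**Inputs for the comparison of methods.** n = 121 per group and two-sided α = 0.05, from the article. The correlation r between baseline and outcome is not given; 0.3, 0.5 and 0.7 are assumed to show a range. Effects are in units of the outcome SD, which is also not given. The SD is taken as equal at baseline and follow-up, with a common linear slope.

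**Formulas**, with the variance of the final-score t test set to 1:
- ANCOVA: 1 − r²
- change-score t test: 2(1 − r)
- ANCOVA relative to change score: (1 − r²) / [2(1 − r)] = (1 + r)/2
- unadjusted group size with the same precision: 121 divided by the variance ratio

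| | r = 0.3 | r = 0.5 | r = 0.7 |
|---|---|---|---|
| Variance, final-score t test | 1 | 1 | 1 |
| Variance, change-score t test | 1.40 | 1.00 | 0.60 |
| Variance, ANCOVA | 0.91 | 0.75 | 0.51 |
| Cut by ANCOVA against final score | 9% | 25% | 49% |
| Equivalent n per group against final score | 133 | 161 | 237 |
| Cut by ANCOVA against change score | 35% | 25% | 15% |
| Equivalent n per group against change score | 186 | 161 | 142 |

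**Power.** The difference that a final-score t test detects with 90% power is √(2/121) × (1.96 + 1.282) = 0.417 SD. At that same true difference (normal approximation):

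| | r = 0.3 | r = 0.5 | r = 0.7 |
|---|---|---|---|
| Final-score t test | 90% | 90% | 90% |
| Change-score t test | 78.2% | 90.0% | 98.7% |
| ANCOVA | 92.5% | 96.3% | 99.5% |

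**Chance imbalance.** The difference in mean baseline score between groups has standard error √(2/121) = 0.129 SD, so its 95% range is ±0.25 SD. An imbalance at that limit shifts a final-score estimate by r × 0.252 = 0.08, 0.13 or 0.18 SD at r = 0.3, 0.5 or 0.7. It shifts a change-score estimate by (1 − r) × 0.252 = 0.18, 0.13 or 0.08 SD in the opposite direction. ANCOVA removes this shift if the linear slope is right.

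**The case against.** The strongest reply is that this is a question of efficiency and not an error. With 1:1 randomization the t test is unbiased, and its confidence interval already allows for chance imbalance. That stands. A reader might infer from the lack of adjustment that the planned estimate is biased or the test invalid; the documents do not support that.

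A second reply is that the t test may be meant for change scores, in which case baseline is not ignored. That is possible, because the text is silent. It alters the size of the gain but not its direction: (1 + r)/2 is below 1 for every r below 1.

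A third is that the size rests on an assumed correlation. That also stands. With intermittent disease enrolled and follow-up running to 16 weeks after baseline, r could be lower. At r = 0.2 the cut against final scores is 4%, equivalent to 121/0.96 = 126 per group.

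Some further readings are tempting but go beyond the text:
- That the t test takes each visit in isolation. No visit is named for it, and a t test can be applied to a per-patient summary.
- That patients with a missing score are dropped. The article plans ITT and PP analyses when patients withdraw, and the handling of missing scores may properly sit in the full protocol or SAP.
- That several run-in VAS scores can be averaged as the covariate. The two-weekly recording over the whole trial may include the run-in, but the diaries are described at baseline and after randomization. Five four-weekly RQLQ assessments span 4 × 4 = 16 weeks, which fits a start at randomization rather than at screening of a 20-week study.
- That persistent or intermittent type is available as a covariate. The article does not describe classifying patients on entry.

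It might also be said that method detail belongs in the SAP. Here, however, the article names the method, so the point concerns what is fixed and not what is absent.

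**Conclusion.** The point holds as a matter of precision. The article fixes a comparison without a baseline covariate for two outcomes whose baseline scores it collects, and it uses baseline only for a test that informs nothing. Under the stated assumptions (r from 0.3 to 0.7, equal SDs, linear relation, 121 per group), ANCOVA has 9% to 49% less variance than a final-score t test and 15% to 35% less than a change-score t test. At r = 0.5 the cut is 25% either way. These figures illustrate what is at stake and are not forecasts, because the documents give neither the correlation nor the SD. The change should be made, but the trial's validity does not depend on it.

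**What to change.** For VAS and for RQLQ, replace the two-sample t test by a linear model of the post-treatment score on treatment and the pre-randomization score of the same measure. Report the adjusted difference between groups with its 95% CI, and fix the model before the group codes are opened. Remove the baseline significance tests as a step in testing the hypothesis and tabulate baseline characteristics by group descriptively.

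The cost is a change of wording and one residual degree of freedom out of 242 − 2 = 240. No patient, visit or measurement is added. The model does assume a linear relation with baseline, so it has to be specified in advance.

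A baseline-adjusted repeated-measures model over the later assessments is an optional extension. It can use partial follow-up data, but it brings assumptions about covariance and missingness at random. A mean of run-in VAS scores, or rhinitis type, should enter as a covariate only if it is in fact recorded before randomization.
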